### Trial design

After completing the baseline survey on tobacco use, physical health, and mental health, we will use a two-arm study design to randomize 60 patients to counseling + NRT (standard care) or counseling + EC. Participants will receive four counseling sessions in 12 weeks; each session will follow a study visit monitoring any physical or mental changes and side effects from using NRT or EC. All participants will complete a follow-up survey at 24 weeks (Fig. 1). During the 12 weeks of study participation, participants will report their tobacco use daily by responding to automated text messages serving as a smoking diary. We will also invite 20 participants for an in-depth interview on their study experience, outcome expectations, EC perceptions, and barriers to smoking cessation.

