#### Outcomes

Our primary outcomes include: (1) feasibility of intervention, and (2) acceptability of intervention. Secondary outcomes include: (1) change in number of self-reported CC per day based on daily reports that are provided for 84 days post-baseline and (2) change in pulmonary symptoms based on CAT scores at 12 weeks.

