#### Randomization

After eligibility screening, participants will be randomized into one of the two study arms (EC or NRT; ratio 1:1) using minimization methodology. This approach has been found to achieve significantly better covariate balance than other randomization methods with a small sample size [30]. Randomization will be stratified by three key variables CAT score (10–19 and ≥ 20), CPD (< 20 and ≥ 20), and sex and will occur using a REDCap based system which includes verification of eligibility criteria prior to the assignment of a study ID and intervention group. Due to the nature of the study, participants are not blind to their randomization allocation.

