#### Statistical methods

Before addressing the study aims, data will be summarized numerically using descriptive statistics. Comparison of the baseline characteristics between the study arms will be performed using chi-square tests for categorical data and t-tests or nonparametric tests for ordinal or continuous data. Preliminary analyses will investigate possible differences on the primary outcomes by gender and race/ethnicity. If differences appear, race/ethnicity and/or gender will be entered as covariates. Exploratory analyses will be conducted where appropriate to better understand the findings. Otherwise, analyses will collapse across race/ethnicity and gender. All data will be presented in aggregate and de-identified prior to publication.

Feasibility and acceptability will be summarized using descriptive statistics. Simple logistic regressions, including ordinal and multinomial models, will be used to compare the characteristics of participants reporting high and low acceptability. We will evaluate the impact of EC vs. NRT on the reduction in self-reported CPD and CAT Score, at 12 and 24 week follow-up assessments, with and without the addition of covariates. CPD at baseline and 12 weeks will be extracted from EMA data, while the 24-week follow-up will be self-report from the telephone survey. The impact of EC vs. NRT on change in CPD and CAT Score will be estimated using a Poisson or negative binomial regression model [47] with follow-up CPD/CAT Score regressed on baseline CPD/CAT Score and an indicator variable of study condition (EC vs. NRT).

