This study is not meant to provide a definitive test of intervention efficacy and will be used to inform future sample sizes for a larger trial [48, 49]. In the primary analysis the sample size is anticipated to provide 80% power to detect a difference of 0.73 points in intervention satisfaction between study arms. For other primary measures, the sample size is anticipated to provide exploratory results to examine observed trends, but not statistically significant difference. For secondary analyses of effectiveness, in a Poisson generalized linear model for the number of CC reduced from baseline to follow-up, we will have greater than 90% power to detect a rate ratio of RR = 1.60 (e.g., a reduction by 5 CC per day in the NRT condition vs. 8 in the EC condition). If there is marked overdispersion of the number of CC per day reduced (κ = 0.2), we will still have greater than 80% power to detect RR = 1.80 (e.g., 5 vs. 9 CC per day reduction). Similarly, without considering covariates, we have 80% power to detect a difference of at least 2.7 on the CAT score, and with effective covariates, we have 80% power to detect a difference of 2.2. Translated to standardized mean differences, these are modest effects (d = 0.33 and d = 0.26). In secondary analyses, we will consider CPD collected daily over a 14-day period prior to the end of the 12-week follow-up. This will increase the power by increasing sample size providing for greater than 90% power to detect a rate ratio of RR = 1.20 (e.g., a reduction by 5 CC per day in the NRT condition vs. 6 in the EC condition). If there is marked overdispersion of the number of CC per day reduced (κ = 0.2), we will still have greater than 80% power to detect RR = 1.40 (e.g., 5 vs. 7 CC per day reduction).

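### The 14-day power claim credits repeated days with adding sample; over 90% power at RR = 1.20 holds only if participants barely differ from one another

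*Protocol article*

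**What the plan says.** All the power statements are in Statistical methods. After the figures for a single baseline-to-follow-up comparison, the protocol adds a further secondary analysis: "we will consider CPD collected daily over a 14-day period prior to the end of the 12-week follow-up". It then states: "This will increase the power by increasing sample size providing for greater than 90% power to detect a rate ratio of", with the effect given as "RR = 1.20 (e.g., a reduction by 5 CC per day in the NRT condition vs. 6 in the EC condition").

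The next sentence is a sensitivity case, opening "If there is marked overdispersion of the number of CC per day reduced (κ = 0.2"). Here the plan claims more than 80% power for RR = 1.40, that is, reductions of 5 versus 7 per day.

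Trial design fixes the sample: "we will use a two-arm study design to randomize 60 patients to counseling + NRT (standard care) or counseling + EC". Randomization sets the ratio at 1:1, so there are 30 per arm. The treatment effect is to be "estimated using a Poisson or negative binomial regression model", with follow-up regressed on baseline and arm. The 14-day sentence names no model, data layout or treatment of within-person correlation.

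**The concern.** The reason given for the extra power is wrong as stated. A participant who reports on 14 days is one randomised unit measured more precisely, not 14 units. Precision from added days is bounded by how much people differ in their average reduction, and added days do not shrink that part.

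The RR 1.20 figure carries no condition about between-person variation, so it reads as a gain that daily texting delivers by itself. The pilot is meant to inform the sample size of a larger trial. If the idea that daily reports enlarge the sample were carried forward, that trial could be planned too small.

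**Working it through.** **Inputs.** From the protocol: 60 randomised 1:1, so 30 per arm; 14 days; mean reductions of 5 versus 6 (RR 1.20) and 5 versus 7 (RR 1.40) per day; κ = 0.2. Assumed, because the power paragraph does not state them: two-sided alpha of 0.05 and no dropout (20% as sensitivity).

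**Formula.** With κ as the between-person variance on the relative scale and Poisson day-to-day noise:

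Var(ln RR) = [(κ + 1/(14·m₁)) + (κ + 1/(14·m₂))] / 30, and power = Φ(ln RR / SE − 1.96).

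**Step 1: the plan's own figures.**
- RR 1.20, κ = 0: Var = (1/70 + 1/84)/30 = 0.000873, SE = 0.0295, ln 1.20 = 0.182. Power is above 99.9%, so the over-90% statement is met when there is no between-person variation.
- RR 1.40, κ = 0.2 at person level: Var = (0.4 + 1/70 + 1/98)/30 = 0.01415, SE = 0.119, ln 1.40 = 0.336. Power is 80.7%, matching the stated figure. A gamma-Poisson simulation (4,000 trials) gave 80.8% with a normal and 79.8% with a t critical value.
- If κ = 0.2 were independent across 420 rows per arm, RR 1.40 would have essentially 100% power, and 80% power would already be reached at RR 1.13. The 1.40 figure therefore fits a calculation that respects the person.

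**Step 2: RR 1.20 as people differ.**

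| κ (person level) | Power at RR 1.20 |
|---|---|
| 0 | >99.9% |
| 0.034 | 90% |
| 0.05 | 80% |
| 0.10 | 56% |
| 0.20 | 33% |
| 0.50 | 16.5% |

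At κ = 0.2: Var = (0.4 + 1/70 + 1/84)/30 = 0.01421, SE = 0.1192, 0.1823/0.1192 − 1.96 = −0.43, so power is 33% (simulation 33–35%).

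Threshold for 90%: SE must not exceed 0.1823/(1.96 + 1.2816) = 0.0562. Then 2κ = 30 × 0.0562² − (1/70 + 1/84) ≈ 0.0687, so κ ≈ 0.034 and CV = √0.034 ≈ 0.18 to 0.19.

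**Step 3: what more days can buy.** With unlimited days at κ = 0.2, Var falls only to 0.4/30 = 0.01333 (SE 0.1155), and power at RR 1.20 is Φ(0.1823/0.1155 − 1.96) ≈ 35%. The days do help: at κ = 0.2 the RR detectable with 80% power falls from about 1.55 (one day) to 1.40 (14 days). They cannot go much further.

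**Step 4: detectable effects at κ = 0.2.** With 60 evaluable: RR 1.40 at 80% power and 1.47 at 90%. With 48 evaluable (20% loss assumed): Var at RR 1.45 = (0.4 + 1/70 + 1/101.5)/24 = 0.01767, SE = 0.133, power about 80%. RR 1.40 then has about 72%.

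**Step 5: conditional check on type I error.** This applies only if daily rows were fitted as independent. At 5 per day and κ = 0.2:
- Poisson rows: the true variance is 1 + 0.2 × 5 × 14 = 15 times the model's, giving 2Φ(−1.96/√15) = 61% (simulation 62%).
- Negative binomial rows: the ratio is (70 + 0.2 × 4900)/(14 × (5 + 0.2 × 25)) = 7.5, giving 47%.
- One total per person: about 5% in the simulation.

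**The case against.** **The plan already gives the overdispersed case.** This is the strongest point, and it stands. RR 1.20 is offered for the plain Poisson case, and the following sentence gives RR 1.40 at κ = 0.2. A reader might infer that the plan claims over 90% power at RR 1.20 under its own overdispersion; it does not. The 33% shows how much the first figure depends on its assumption. It does not contradict a claim the plan makes.

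**The source of the RR 1.20 figure is unknown.** With no heterogeneity even RR 1.10 has about 90% power, so some allowance for clustering may have been made. For example, an intraclass correlation of 0.20 gives 420/(1 + 13 × 0.20) = 117 effective observations per arm and 90% power. That is fair, and one should not assert that zero variation was used. But it leads to the same place: on a Poisson variance of 5, it implies a between-person variance of 0.20 × 5 = 1, or κ = 1/25 = 0.04. The figure still needs people who hardly differ. Likewise, person-level κ is not the only route to the RR 1.40 figure: an intraclass correlation of 0.5 with row-level κ = 0.2 gives 83%.

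**Baseline adjustment could lower the residual κ.** True, and the 33% makes no allowance for it. It would have to bring κ to about 0.034, although individual responses can range from no change to quitting.

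**No model on daily rows is stated.** A reader might infer from the sample-size wording that 840 person-days will be analysed as independent. The protocol does not say so. Its named regression reads as one follow-up value per person, and the repeated-measures detail may be in an analysis plan not shown. The type I error figures are therefore a warning and not a finding.

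**The CPD windows do not conflict.** A reader might also set the 14-day window against the outcome definition, "change in number of self-reported CC per day based on daily reports that are provided for 84 days post-baseline". One describes the diary data and the other is labelled a secondary analysis, so they are compatible.

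**Conclusion.** The point holds in a limited form. The stated rationale is wrong, because repeated days from 60 people do not add sample. The over-90% power for RR 1.20 rests on an unstated condition of near-identical participants, with person-level κ of about 0.034 or less. Power is 80% at κ = 0.05 and 33% at κ = 0.2. The RR 1.40 figure is sound at about 81%. These results assume two-sided alpha of 0.05, 30 evaluable per arm, a reduction of 5 per day in the NRT arm, Poisson daily noise and no gain from baseline adjustment.

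Both printed inequalities can be reproduced, so this is not an arithmetic slip. Nor do the documents support saying that the planned analysis has an inflated type I error. Severity is moderate to minor: the primary outcomes are feasibility and acceptability, the effect aims are declared exploratory, and the protocol disclaims a definitive efficacy test.

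**What to change.** In Statistical methods:

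1. Delete the words that attribute the gain to a larger sample. Say instead that averaging over 14 days reduces within-person noise.
2. Remove the RR 1.20 statement, or label it as the case without between-person variation.
3. Lead with the overdispersed case: at κ = 0.2 and two-sided alpha of 0.05, about RR 1.40 at 80% power and 1.47 at 90% with 60 evaluable, or about 1.45 at 80% with 48 evaluable if 20% loss is assumed.
4. State that the participant is the unit of analysis. Either use one 14-day total per person with an offset for the log of days reported, or use daily rows with a participant random intercept or participant-clustered standard errors.

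The cost is a few sentences and one model line. Design, sample size and data collection do not change. The only downside is a less favourable stated power.

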##### Qualitative data analysis

Data collected from interviews will be recorded and transcribed for analysis. Data will be coded according to the principles of the framework for applied policy research [50]. Directed content analysis technique with deductive coding will be used [51]. The developed codes will represent each of the relevant constructs with additional codes developed from themes arising from the data, using the principles of grounded theory [52]. Interview transcripts will be analyzed with Atlas.ti 9.0 for thematic analysis [53]. Inter-coder reliability will be calculated using the first two transcripts. Disagreements will be discussed and additional transcripts will be reviewed until 90% inter-coder reliability is achieved. When coding is complete, the outputs of quotations with each code will be examined and summarized into themes. A sample of 20 interviews was determined a priori to potentially achieve theme saturation [54].

#### Harm

EC are not deemed risk free, with some studies suggesting adverse pulmonary effects [21, 22], and some brands of the liquid nicotine contain toxicants and carcinogens found in CC [55–57]. To address these concerns any minor or major events associated with the intervention or NRT arms will be screened for through survey and open-ended questions. At each study visit, participants will be asked about any changes in their medical status, potential side effects of NRT/EC use, psychological distress [58], nicotine withdrawal [59], and in the intervention arm EC dependence will be assessed [60]. Any adverse events or unintended effects detected will be reviewed by a researcher and a study physician.

## Discussion

Among those with COPD who smoke, the most effective means of slowing COPD progression is smoking cessation [5, 6]. In spite of decades of progress in tobacco control, nearly half of people with COPD still smoke CC [8]. The overarching aim of this study is to address the unmet need for feasible and effective strategies for reducing CC use among those with COPD, which has the potential to significantly improve the health of those with COPD who smoke. EC could provide an additional tool for harm reduction in adult smokers who have greater difficulty quitting. This research has implications for both the clinical treatment of COPD as well as public health tobacco use treatment policy. The data from this pilot study will provide the foundational knowledge necessary to determine the feasibility of an EC harm-reduction intervention in this population and inform modifications to intervention counseling tools to address the specific needs of this population. If found to be feasible and acceptable, a fully powered trial is anticipated and the counseling program will be manualized.

EC may lead to more use than traditional NRT. Despite 30–40 years of availability, smokers often have very limited enthusiasm for NRT, and decades of interventions have not had a large impact on that. Claims that EC are a harm-reducing alternative to smoking resonate among current smokers [61–64]. In addition, smokers often prefer the experience of using EC compared to CC [65], and there are indications that many smokers find EC more appealing than other smoking cessation aids (such as NRT) [9–11]. This preference indicates the population reach and impact of EC could prove greater than traditional pharmacotherapies.

The relative harm of EC is significantly less than CC, and the public health implications of adult smokers switching to EC are great. While not without some health risks [66–68], all available evidence indicates that EC are safer than CC. There is strong evidence suggesting that the benefits of EC helping with CC cessation and harm reduction substantially outweigh their potential harm [18, 23, 24]. Unlike CC, EC are not associated with coronary heart disease or myocardial infarction [69]. Replacing most CC use with EC use in the US could result in 1.6–6.6 million fewer premature deaths and 20.8–86.7 million fewer life-years lost over a 10-year period [24]. While EC uptake by adolescents is of great concern, this modelling study found that the gains in adults outweighed the harm in adolescents by a large margin in all sensitivity analyses. Warner and Mendez similarly found that over a wide range of plausible parameters, “potential life-years gained as a result of vaping-induced smoking cessation are projected to exceed potential life-years lost due to vaping-induced smoking initiation” [18]. However, few studies have looked at the extent to which smokers will substitute EC for CC, and these studies have been small [70, 71].

A harm reduction approach with the goal of achieving CC switching may be a more pragmatic approach, making EC use particularly appropriate with COPD [25]. EC represent a potentially effective harm reduction tool that is safer than smoking CC [18, 23, 24]. Smokers with COPD, however, tend to be older and may have a higher level of addiction to nicotine than the average smoker and the feasibility and preliminary effectiveness of an EC harm-reduction strategy in a COPD population has not been explored. More research is needed to evaluate the role of EC in the smoking patterns of adults and the impact of switching from CC to EC in people with COPD. This pilot study will serve to fill these knowledge gaps and provide the groundwork for future research in this area.

Our study protocol has a few limitations. First, as a pilot study the protocol is not powered to detect small differences in CPD or CAT Scores between the NRT and EC arms. Second, CAT Score is not the gold standard for the assessment of respiratory health. If this study is successful, future research needs to include assessment of airflow by spirometry, as well as by assessment of small airway function using respiratory oscillometry. While FEV1 change is not typically observable in early stage COPD patients, oscillometry may identify the presence of small airway injury in this population [72]. Adherence to study medications is not directly measured, therefore analyses are limited to intent-to-treat rather than per-protocol. The NJOY EC used in the study is not representative of all EC available and additional research using alternate products is called for. EC contain nicotine, which is an addictive substance and therefore there is potential for participants to continue EC use after the study is complete. The counseling protocol does not include EC cessation. Future research on EC cessation methods and continued EC use after switching is called for. Finally, all study measures are self-report. Future studies should include bio-confirmation of CC reduction such as CO.

## Data Availability

Not applicable.
